## Abstract

**Background:**

Treatments for youth mental disorders are a public health priority, especially in sub-Saharan Africa (SSA), where treatment options remain limited due to high cost, elevated stigma, and lack of trained mental health professionals. Brief, accessible, and non-stigmatizing community-based interventions delivered by lay providers may help address treatment needs in SSA. One such intervention, the Shamiri Intervention, consisting of three elements (growth mindset, gratitude, and value affirmation) has been tested in randomized controlled trials with school-going Kenyan adolescents. This three-element Shamiri Intervention has been shown to significantly reduce depression and anxiety symptoms and improve social support and academic performance relative to a control group. In this trial, we aim to investigate the effects of each element of the Shamiri Intervention.

**Methods:**

In this five-arm randomized controlled trial, we will test each of the intervention components (growth mindset, gratitude, and value affirmation) against the full Shamiri Intervention and against a study skills control intervention. Students (*N*_planned_ = 1288) at participating secondary schools who are interested in participating in this universal intervention will be randomized in equal numbers into the five groups. The students will meet in groups of 8–15 students led by local high school graduate lay providers. These lay providers will receive a brief training, plus expert supervision once a week throughout the intervention delivery. Multi-level models will be used to compare trajectories over time of the primary outcomes (depressive symptoms, anxiety symptoms, academic performance, and wellness) and secondary outcomes in each intervention group to the control group. Multi-level models will also be used to compare trajectories over time of the primary outcomes (depressive symptoms, anxiety symptoms, academic performance, and wellness) and secondary outcomes of participants in the single-element interventions compared to the full Shamiri Intervention. Finally, effect sizes (calculated as mean gain scores) will be used to compare all groups on all measures.

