## Methods: participants, interventions, and outcomes

### Study setting {9}

The study will take place in high schools (i.e., secondary schools); we will seek up to 12 schools in the Nairobi, Kiambu, Machakos, Makueni, and neighboring counties in Kenya, to fill the target sample of 1288 students (see “Sample size” section below). Care will be taken to select a variety of schools: day and boarding schools, boys and girls schools, and, if possible, mixed-gender schools, and schools with a variety of rankings and incomes (for example, some schools ranked as “National” schools and others ranked as “County” or “Sub-County” schools; see [3] for more). A full list of study sites will be available on PACTR: https://pactr.samrc.ac.za/TrialDisplay.aspx?TrialID = 14677.

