### Sample size {14}

We conducted a power analysis using Optimal Design, a statistical simulation software which can estimate sample size for randomized controlled trials assessed using multi-level (i.e., mixed effects) models [74]. In Optimal Design, we estimated the required sample size for a person-randomized trial with six-time repeated measures (baseline, midpoint, post, 1-month follow-up, 3-month follow-up, 6-month follow-up, and 9-month follow-up). Additionally, for each outcome measure, we have four contrasts of primary interest (each intervention condition compared to the control), thus, using a conservative *p* value correction, we would divide the typical alpha value of .05 by four and get a *p* value threshold for significance of .0125. Finally, we assumed that we are interested in detecting a minimum post-treatment effect size of .3. We selected this value for the following reasons: 1) it is slightly lower than the effect sizes found in most previous trials of Shamiri, which range from .32–.83 at the latest follow-up points [3, 20, 33, 34], which will allow us to detect potentially smaller effects of the individual component interventions, and to detect effects in a universal sample, and 2) a standardized effects size of .3, which is considered small to medium, remains clinically meaningful and important in our view, whereas a change smaller than that may not be as clinically meaningful. Given these parameters, we found that a sample of 515 students would be needed to conduct a two-group trial with a power of .80. So, for this five-group trial, we multiplied that by 2.5, to get a final target sample size of 1288 students. Because in a past trial with 7-month follow-up there was a high dropout rate during follow-up of up to 40% [33], we will initially invite 2147 students to the sessions, assuming that around 40% of them will drop out prior to the sessions or during the follow-up period.

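### The abstract gives 1288 as the number randomised, but the sample-size section needs about 1288 left after around 40% loss from 2147 invited, and the planned number randomised is never stated

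*Protocol article*

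**What the plan says.** The number 1288 appears in three places in the protocol article.

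- **Abstract, Methods.** The planned N of 1288 is the count of students who "will be randomized in equal numbers into the five groups". Here 1288 is the number randomised.
- **Sample size {14}.** The calculation starts from a two-group trial: "we found that a sample of 515 students would be needed to conduct a two-group trial with a power of .80". It is scaled to five arms: "we multiplied that by 2.5, to get a final target sample size of 1288 students". Loss is dealt with afterwards: "we will initially invite 2147 students to the sessions, assuming that around 40% of them will drop out", either before the sessions or during follow-up. Here 1288 is what is left after loss.
- **Study setting {9}.** Up to 12 schools are sought "to fill the target sample of 1288 students", with a cross-reference to the sample-size section.

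Participant timeline {13} puts consent and baseline assessment first, then allocation, then the first session. Statistical methods {20a} defines the intent-to-treat set as everyone who consents, is randomised and completes baseline measures.

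**The concern.** One number is given two roles. The sample-size section combines loss before the sessions with loss during follow-up. The second kind follows allocation by definition, so if any of it occurs the number randomised must exceed the number remaining. The abstract makes them the same.

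The stated power is at stake. The .80 belongs to about 1288 students contributing data. A team that took the abstract at face value and stopped at 1288 randomised would have no reserve for the attrition that the sample-size section itself expects. A later reader also could not tell whether 1288 randomised meant that recruitment was complete or well short of plan.

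**Working it through.** **Inputs, all from Sample size {14} unless noted**

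- Effect: "detecting a minimum post-treatment effect size of .3", taken as a standardised difference (SD = 1).
- Alpha: "divide the typical alpha value of .05 by four and get a" threshold of .0125. Sidedness is not stated; two-sided is assumed.
- Two-group N = 515 (257.5 per arm) at power .80.
- Five-arm N = 1288; invited = 2147; loss around 40%.
- Equal allocation to five arms (Trial design {8}), so 1288/5 = 257.6 per arm.

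**Step 1. Reproduce the plan's figures**

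- 515 × 2.5 = 1287.5, rounded to 1288.
- 1288/(1 − 0.40) = 2146.7, rounded to 2147. In reverse, 2147 × 0.60 = 1288.2.
- Power for two means, normal approximation: Φ(d·√(n/2) − z), with z = 2.498 for two-sided .0125. At n = 257.5 per arm: 0.3 × √128.75 = 3.404, and Φ(3.404 − 2.498) = .82. The noncentral t gives .815. Both are close to the stated .80.
- Solving for N at power .80 gives 496 in total (normal) or 500 (t), near 515. One-sided .0125 gives 424 and two-sided .05 gives 350. Neither fits, which supports the two-sided .0125 reading.

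The arithmetic of the sample-size section is therefore sound, and it fixes 1288 as the number after loss.

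**Step 2. Power if only 1288 are randomised**

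Students remaining per arm are 257.6 × (1 − loss after randomisation).

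| Loss after randomisation | Remaining per arm | Power (normal approx.) |
|---|---|---|
| 0% | 257.6 | .82 |
| 10% | 231.8 | .77 |
| 20% | 206.1 | .71 |
| 30% | 180.3 | .64 |
| 40% | 154.6 | .56 |

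The noncentral t gives .815 at 0%, .70 at 20% and .55 at 40%. Calibrating so that 515 gives exactly .80 changes the 20% and 40% values to .69 and .54.

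**Step 3. Detectable effect at 40% loss**

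1288 × 0.60 = 772.8 remain, or 154.6 per arm. Then d = (2.498 + 0.842) × √(2/154.6) = .38 for power .80. The noncentral t also gives .38.

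**Step 4. What number randomised would leave 1288?**

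This depends on how the 40% divides between loss before and after randomisation, which the protocol does not say. The required number is 1288/(1 − loss after randomisation): about 1431 at 10%, 1610 at 20% and 2147 at 40%. It equals 1288 only if nobody is lost after randomisation, contrary to the sample-size section's own assumption of follow-up dropout.

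**The case against.** The strongest reply is that the sample-size section already plans for attrition, so a shortfall arises only if someone follows the abstract and ignores that section. That is fair as to consequence, but it leaves the two statements in conflict.

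Three stronger readings are tempting, and the documents do not support them.

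- **That power is .55 rather than .80.** The .55 is a worst case. It needs the whole 40% to fall after randomisation and students who drop out to contribute nothing. The plan's 40% mixes two kinds of loss, and its source is a rate of up to 40% in an earlier trial with 7-month follow-up. Statistical methods {20a} and the missing-data section {20c} keep all eligible randomised students in mixed models with multiple imputation, so partial data count. Results to 1 month are likely to be analysed first (Interim analyses {21b}), when attrition may be lower. School grades, one of the four primary outcomes, are still collected after discontinuation following the first session unless consent is withdrawn {18b}. The two-sample formula is also only a proxy for the repeated-measures calculation in Optimal Design, whose remaining inputs are not given.
- **That 2147 is the number randomised.** Being invited to sessions that follow allocation points that way, but the text says invited, not randomised. Loss before the sessions could fall on either side of allocation, and attention checks and group capacity limit entry (Eligibility criteria {10}). The number could lie anywhere between 1288 and 2147. A fixed gap of 859 in the intent-to-treat denominator is likewise not established.
- **That Study setting {9} independently repeats the abstract's figure as a stopping rule.** It refers to the sample-size section and sets no rule for stopping at 1288. It needs aligning, but it is not second evidence of the conflict.

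**Conclusion.** The inconsistency stands. The abstract uses 1288 as the number randomised. The sample-size section uses it as the number remaining after around 40% loss from 2147 invited. Because some of that loss is follow-up loss, both cannot hold, and the planned number randomised is missing.

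The consequence is conditional. If only 1288 were randomised, power per contrast would be about .70 with 20% loss after randomisation and could fall to about .55 (detectable d about .38) with the full 40%, against the stated .80. These figures assume a two-sample comparison at d = .3 and two-sided alpha .0125, no information from students who drop out, and no clustering. They show the possible size of the shortfall and do not estimate the trial's actual power. If enough students are randomised to leave about 1288, the planned power is unaffected by this point and only the wording is wrong.

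**What to change.** State two numbers and label each: the planned number randomised, and the roughly 1288 (about 258 per arm) expected with final follow-up data. If everyone invited to the sessions is to be randomised, the first is about 2147 (about 429 per arm). If some of the 40% is expected before allocation, it is lower, and the assumed split should be given. Use both numbers consistently in the abstract, Study setting {9} and Sample size {14}.

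If only 1288 will in fact be randomised, restate the power or the detectable effect for the assumed loss after randomisation, preferably by rerunning the original repeated-measures calculation rather than adopting the approximation used here.

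In the first case the cost is a few sentences and no students beyond those already to be invited. In the second it is one recalculation and a revised power statement.

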**Discussion:**

This trial will shed light on the mechanisms and outcomes targeted by each individual intervention, helping prioritize which mental health interventions are most important to disseminate.

**Trial registration:**

PACTR Trial ID: PACTR202104716135752. Approved on 4/19/2021.

**Supplementary Information:**

The online version contains supplementary material available at 10.1186/s13063-021-05736-1.

## Administrative information

Note: the numbers in curly brackets in this protocol refer to SPIRIT checklist item numbers. The order of the items has been modified to group similar items (see http://www.equator-network.org/reporting-guidelines/spirit-2013-statement-defining-standard-protocol-items-for-clinical-trials/).

## Introduction

### Background and rationale {6a}

Many epidemiological studies have shown that common mental health problems are prevalent among adolescents aged 13-to-19 in low-income regions of Sub-Saharan Africa [1–3]. Unfortunately, these youths often cannot access treatment because of barriers such as societal stigma [4], lack of culturally appropriate treatment options [5], the length and cost of traditional treatments [6–8], and a paucity of trained mental health care providers [9]. Because a majority of mental health problems first arise during adolescence and have been shown to impact important future life outcomes [6, 10, 11], there is an urgent need for mental health interventions for youths in SSA where nearly half of the population is aged 19 or younger [12, 13].

Numerous youth interventions have been tested and found to produce beneficial effects [14, 15]. However, most of these interventions focus explicitly on psychopathology and thus could invoke stigma in SSA youths, and most require implementation by professionally trained providers, which are scarce in SSA countries. An alternative approach that may be more appropriate for SSA youths can be found in the emerging science of “character strength” interventions. Interventions that target character strengths (e.g., gratitude, sense of purpose) may circumvent the stigma associated with interventions that target maladaptive cognitions, behaviors, and emotions. Character strength interventions are commonly evaluated as positive psychology interventions [16] as well as “wise” interventions [17] that focus on a specific skill or concept [17–19]. Indeed, a body of research suggests that character strengths interventions may improve adolescent health, development, and academic outcomes. Character strength interventions may be particularly valuable in SSA and other high-stigma, low-resource settings because they are simple and likely low-stigma, meaning that they can overcome limitations including the paucity of mental health experts and societal stigma.

Building on the promising research that has supported the effects of character strength interventions on adolescent mental-health outcomes, our team has focused on developing and testing a simple, scalable, low-stigma, and low-cost intervention called Shamiri (Kiswahili for “thrive”) for Kenyan adolescents [20–22]. The Shamiri intervention includes three empirically supported brief character strength interventions: growth mindset [23–27], gratitude [28–30], and value affirmation [31, 32], which were iteratively adapted through co-design with and feedback from local stakeholders [20, 33] to be appropriate for use in Kenyan high schools. Shamiri is a group-based intervention delivered in naturalistic school settings by lay providers who are recent high school graduates without formal training in mental health [20, 21]. We tested the Shamiri intervention in a randomized controlled trial (RCT) with 51 Kenyan adolescents with clinically elevated depression and/or anxiety symptoms; youths assigned to Shamiri reported significant improvements in depression and anxiety symptoms, academic performance, and perceived social support from friends when compared to youths in an active study skills control group of equal duration [16]. In a well-powered replication (*N* = 413) [21], we found that youths assigned to the Shamiri intervention reported significantly greater improvement in depression and anxiety symptoms than youth in the control group. Effects lasted until the 7-month follow-up period [33]. Besides this, both RCTs showed that the Shamiri intervention was feasible and acceptable for Kenyan youths.

This past work may raise questions about whether the promising effects of the Shamiri intervention are due to the “bundling” together of three-character strength interventions, or whether some character strength interventions are more helpful than others, or even potentially beneficial when used alone. Answering these questions may shed light on the mechanisms and outcomes targeted by each individual intervention, as well as helping prioritize which mental health interventions are most important to disseminate. Previously, we investigated the effects of each element of the Shamiri intervention in a universal, classroom-based microtrial with 2-week follow-up [34]. This trial provided some initial evidence that the value affirmation and growth mindset components may be more effective on their own than the gratitude component, particularly for reducing symptoms of anxiety [34]. However, this trial had several limitations: first, it did not allow for comparison between the individual elements and the three-component Shamiri; second, the trial was cluster-randomized, and therefore underpowered to detect small effects; and third, microtrials are not intended to assess long-term effects. Thus, to build on our existing work, we plan to conduct a large, well-powered randomized controlled trial to compare the longer-term follow-up effects of the combined Shamiri intervention and its constituent character strength interventions (i.e., growth mindset, gratitude, and values), against an active control group.

### Objectives {7}

The objectives of this study are threefold. First, we aim to compare the effects of each intervention and control condition on the primary outcomes (depressive symptoms, anxiety symptoms, academic performance, and wellness). We hypothesize that all the intervention groups will outperform the active control on each primary outcome. Second, we aim to compare the effects of each group on secondary outcomes (described below in {12}). Finally, in an exploratory fashion, we also aim to identify for whom these interventions are most effective and their mechanisms of change.

### Trial design {8}

This study is a parallel-group randomized controlled comparative effectiveness trial with five arms:1) the Combined Shamiri Intervention (consisting of a growth element, a gratitude element, and a value affirmation element; henceforth called “Shamiri”), 2) the Growth Intervention, which encompasses content related to growth mindset and strategies for growth, 3) the Gratitude Intervention, which incorporates content to build feelings of gratitude and expression of gratitude, 4) the value affirmation intervention, which incorporates content to help students identify and better act on their personal values and sense of purpose, and 5) a study skills control group, an active control group teaching students study skills that may be useful to them as students. Each condition is described further below under “interventions.” Participants will be allocated within each school to the five conditions with a 1:1:1:1:1 ratio, or equal probability for assignment to each condition. Each arm will require 4-h-long sessions spanning 4 weeks and will be delivered in a group (8–15 students) setting by a local, trained lay provider between the ages of 18 and 24. Measures of mental health, wellbeing, and character strengths will be collected at baseline, 2-week midpoint, 4-week endpoint, and 1-month, 3-month, 6-month, and 9-month follow-up. Academic data will be collected for the school terms before, during, and after the intervention. De-identified trial data will be available in an online repository and upon request.

## Methods: participants, interventions, and outcomes

### Study setting {9}

The study will take place in high schools (i.e., secondary schools); we will seek up to 12 schools in the Nairobi, Kiambu, Machakos, Makueni, and neighboring counties in Kenya, to fill the target sample of 1288 students (see “Sample size” section below). Care will be taken to select a variety of schools: day and boarding schools, boys and girls schools, and, if possible, mixed-gender schools, and schools with a variety of rankings and incomes (for example, some schools ranked as “National” schools and others ranked as “County” or “Sub-County” schools; see [3] for more). A full list of study sites will be available on PACTR: https://pactr.samrc.ac.za/TrialDisplay.aspx?TrialID = 14677.

### Eligibility criteria {10}

Youths will be eligible for inclusion if they are a student in a participating school between the ages of 12 and 21. This will be a universal intervention and participants will not be screened in any way in, so long as they are in Form 2 and Form 3 (second and third years in high school). Participants who fail attention checks during baseline measures will be excluded. No participant who meets these criteria will be excluded for any other reasons other than the capacity of the groups: should more students than we can have in the group be interested in participation, we will randomly select students to join the groups.

The lay providers delivering the intervention will be eligible if they are living near Nairobi, Kenya, if they attended and graduated from a Kenyan high school, and if they are between the ages of 18 and 24. Among those applicants who meet criteria, the study team will conduct interviews to select those who seem to have the strongest counseling skills, commitment to the project, and understanding of the challenges commonly faced by Kenyan high schoolers. Applicants will first be evaluated via a brief written application, then via 30-min interviews including questions about experiences, motivations, and hypothetical scenarios. Full information about the process of interviewing and evaluating lay provider applicants can be found in [35]. Additionally, the study team will prioritize hiring those between 18 and 22. The recruitment and training process for lay providers in this trial will closely resemble that employed in a previous RCT of the Shamiri Intervention [35].

### Who will take informed consent? {26a}

A member of the study team who is from and living in Kenya (either Co-PI [name] or Co-I [name]) will seek informed consent and assent prior to participant randomization and responses to baseline measures. We will provide all participants with a paper copy of the consent form (see {32} for information about a model consent form). Then, an upper-level member of the study team with appropriate ethical training and IRB approval will walk the participants through the consent form and clarify any questions that they may have. They will emphasize the voluntary nature of participation in the study.

